## Abstract

**Objectives:**

Chronic low back pain has become a major cause of global disability and caused a huge economic burden to society. Physical therapy is a vital strategy for rehabilitation of chronic low back pain. Although several trials have shown that Tai Chi Quan is a beneficial treatment, the comparative effectiveness of Tai Chi Quan versus physical therapy is unknown. We are conducting a randomized controlled trial to assess the effectiveness of Tai Chi Quan versus that of physical therapy in treating chronic low back pain.

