Tai Chi Quan can significantly improve core stability and muscle strength, thereby reducing the risk of falls in patients with CLBP (Lomas-Vega et al., 2017). Sleep problems are common among people with CLBP, and insomnia can increase the risk of CLBP (Skarpsno et al., 2020). A meta-analysis showed that TCQ has a significant beneficial effect on the sleep quality of the elderly (Du et al., 2015). The intensity of TCQ practice depends on time, speed and experience. For the elderly with CLBP, simplified TCQ is easy to learn and can improve balance, coordination and spinal stability. Compared with the waiting group and the usual care group, TCQ from 10 to 28 weeks had a better effect on lumbago (Kong et al., 2016). However, few studies have investigated the long-term follow-up effects of TCQ on CLBP. Although PT is the main management method for LBP rehabilitation, it is expensive in terms of manpower and financial resources. As an easy to learn and low- cost exercise therapy, TCQ is expected to be accepted as an alternative therapy by a large number of patients with CLBP. However, previous studies had some deficiencies, such as short intervention time, lack of follow-up observation and economic analysis, and evidence supporting the application value of TCQ in patients with CLBP remains insufficient. Therefore, we propose a detailed protocol to study the comparative effectiveness of TCQ classes versus grouped-PT for people with CLBP. Our primary hypothesis is that TCQ and grouped-PT have a significant clinical effect on CLBP. The secondary hypothesis is that TCQ is not inferior to PT in terms of improving outcomes. The third hypothesis is that TCQ has a longer-term effect than PT.

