### Sample Size

The sample size analysis is based on hypothesized change in RMDQ scores. For the primary outcome of change in pain intensity from baseline to week 12, we assume that two-sided α error prob is equal to 0.05 and power is 0.8. The minimal clinically important difference of the RMDQ is prespecified for 3 points (Jordan et al., 2006), and the effect size of RMDQ is in the range of 0.54–0.84 (Saper et al., 2017). We used G-Power Software (version 3.1.9.2, Germany) to estimate the total sample size with the method of *t*-tests-means (difference between two independent means measures in two groups). Considering the effect size of RMDQ is 0.54 and 20% attrition rate, we need a minimum of 138 participants in this study or 69 participants in each group to detect whether 12 weeks of TCQ and grouped-PT have a significant clinical effect on CLBP.

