### Data Analysis

Intention-to-treat analysis will be performed regardless of adherence. Microsoft excel 2016 and IBM SPSS Statistics 20.0 (SPSS Inc., Chicago, IL, United States) will be used in data analysis. Continuous variables (e.g., age, body mass index, NRS score, and RMDQ score) will be represented as mean ± standard deviation and be compared using analysis of the independent samples *t*-test. We will use the chi-squared test to analyze the categorical variables (e.g., gender, marital status, smoking, and exercise habits) between the TCQ group and PT group. The baseline demographics characteristics differences between groups will be compared using analysis of *t*-test, variance (ANOVA) or chi-squared tests. If potential confounding factors including gender, age, body mass index, smoking, exercise habits, etc., are present, we will prespecified an adjusted analysis, by using multiple linear regression. At the same time, missing values at week 12, 26, and 52 will be imputed using the multiple imputation.

The co-primary outcomes are the measurement of minimal clinically important difference in NRS and RMDQ scores in two groups after the 12-week intervention, and the paired-sample *t*-test will be carried out for the comparison of the differences. For secondary outcomes, the difference of continuous variables between groups will be compared using the analysis of independent-samples *t*-test. Expenses for LBP or other disease will be explored for cost-benefit analysis. Participants’ global perceived effect, adherence, and health-related quality of life will be compare using appropriate regression. The Fisher exact test will be used to compare adverse events. For the follow-ups phase, two-way repeated-measures analysis of variance (group × time) will be carried out to assess the differences of the primary outcomes (NRS score and RMDQ score) between the two groups. In all analyses, a *P*-value of <0.05 will be considered statistically significant.

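### The week-12 co-primary analysis is a paired t-test, which measures change within each arm and does not compare Tai Chi Quan with physical therapy

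*Protocol article*

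**What the plan says.** All references are to the Protocol article.

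- **Co-primary analysis (Data Analysis).** The outcomes are defined as follows: "The co-primary outcomes are the measurement of minimal clinically important difference in NRS and RMDQ scores in two groups after the 12-week intervention". The same sentence continues: "and the paired-sample *t*-test will be carried out for the comparison of the differences".
- **Secondary outcomes (Data Analysis, same paragraph).** "For secondary outcomes, the difference of continuous variables between groups will be compared using the analysis of independent-samples *t*-test".
- **Other tests that touch NRS and RMDQ (Data Analysis).** A general sentence begins "Continuous variables (e.g., age, body mass index, NRS score, and RMDQ score) will be represented as mean ± standard deviation" and goes on to an independent-samples t-test. Later: "For the follow-ups phase, two-way repeated-measures analysis of variance (group × time) will be carried out", applied to the primary outcomes between the two groups.
- **Primary hypothesis (Introduction).** "Our primary hypothesis is that TCQ and grouped-PT have a significant clinical effect on CLBP". Non-inferiority of Tai Chi Quan (TCQ) to physical therapy (PT) is placed second.
- **Objective (Abstract).** The stated gap is that "the comparative effectiveness of Tai Chi Quan versus physical therapy is unknown", and the trial is meant to fill it. The Discussion repeats the comparative aim.
- **Sample Size.** The G-Power method is a t-test for the "difference between two independent means measures in two groups", with effect size 0.54, two-sided alpha 0.05, power 0.8 and 20% attrition, giving 138 in total or 69 per group.

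**The concern.** A paired t-test needs pairs. No matching of TCQ participants to PT participants is described, so the only pairs available are a person's own baseline and week-12 scores. The designated test therefore asks whether each arm changed from zero. It does not ask whether the arms differ.

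Three consequences follow.

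1. The headline result would not use the randomised contrast, which is the reason for having two arms.
2. Change within an arm has no causal reading here. There is no untreated arm, and entry requires average NRS of 3 to 8 and RMDQ of at least 5. Regression to the mean and natural course could produce improvement in both arms whatever the treatments do.
3. The outcome is framed around the minimal clinically important difference (MCID), but rejecting zero change does not show that the MCID was reached.

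**Working it through.** **Inputs from the Sample Size section:** d = 0.54; two-sided alpha 0.05; power 0.80; attrition 20%; N = 138; RMDQ MCID 3 points.

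**Assumptions not in the document:** SD of RMDQ change of 4 to 6 points; and, where stated, 0.54 read as a standardised within-arm change.

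**Step 1. Reproduce the plan's figure.** A two-sample t-test (noncentral t) with d = 0.54 needs 54.8, so 55 per arm and 110 in total. With attrition, 110 / (1 − 0.20) = 137.5, so 138, or 69 per arm. The stated N is reproduced, and it belongs to a between-arm test. With 55 completers per arm the power of that test is 0.801.

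**Step 2. What the paired test would have needed.** With 0.54 taken as the standardised within-arm change (assumption), a paired test at 80% power needs 28.9, so 29 completers per arm; 29 / 0.80 = 36.25, so 37 enrolled per arm. With 55 completers its power is 0.976. The stated 80% therefore does not describe the designated test.

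**Step 3. Smallest within-arm change that is significant.** This is t(0.975, 54) / √55 = 0.270 SD of change.

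- SD 4: 0.270 × 4 = 1.08 points.
- SD 6: 0.270 × 6 = 1.62 points.

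Relative to the 3-point MCID these are 36% and 54%. (The RMDQ outcome section expresses the MCID as a 30% reduction from baseline instead; that equals 3 points only at a baseline of 10.)

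**Step 4. What paired results would say about TCQ versus PT.** If both arms have the same true standardised change of 0.54, both paired tests are significant with probability about 0.976² = 0.95. A simulation (55 per arm, normally distributed change with SD 1, 20,000 runs) gives:

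| True standardised change, arm 1 / arm 2 | Both paired tests significant | Between-arm t-test significant |
|---|---|---|
| 0.54 / 0.54 | 95.5% | 5.1% |
| 0.84 / 0.54 | 97.5% | 34% |

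The paired result is nearly the same whether or not the arms differ.

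**The case against.** **The paired test fits the primary hypothesis.** This is true. The hypothesis says that both treatments have an effect, and the last sentence of the Sample Size section describes the purpose in the same way. Test and hypothesis are consistent with each other. But the pair conflicts with the objective and with the two-independent-means calculation, and the hypothesis as worded cannot be established without an untreated arm.

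**NRS and RMDQ are compared between arms elsewhere.** A reader might infer that pain and function are never compared between arms; the text does not support that. The general sentence assigns an independent-samples t-test to continuous variables including NRS and RMDQ, and the group × time ANOVA covers the primary outcomes in follow-up. However, the general sentence gives no time point and lists these scores beside age and body mass index, and the ANOVA is tied to the follow-up phase. Neither is designated as the week-12 co-primary analysis. These sentences soften the point without resolving it.

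**It could be a slip of the pen.** The next sentence gives secondary outcomes an independent-samples test between groups, so the text does distinguish the two tests.

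**One arm significant and the other not.** A reader might expect this to happen often. With equal true effects and 80% within-arm power, the chance would be 2 × 0.8 × 0.2 = 32%. At the 97.6% power of Step 2 it is only 2 × 0.976 × 0.024 = 4.7%. The document fixes no within-arm power, so neither figure is a forecast. The likelier problem is two significant arms that say nothing about the comparison.

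**Conclusion.** The concern holds, confined to the designated week-12 co-primary analysis. As written, that analysis tests within-arm change, while the objective and the sample size are for a between-arm comparison.

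That only within-arm pairs exist, that 138 comes from a two-sample calculation, and that significance starts at 0.27 SD with 55 completers all follow from the document. The translation to 1.1 to 1.6 RMDQ points depends on the assumed SD of 4 to 6. The 97.6% and roughly 95% figures depend on reading 0.54 as a within-arm standardised change; the Sample Size section uses it in a two-group calculation. That regression to the mean and natural course will improve both arms is plausible but not certain; what is certain is that the design cannot separate them from treatment.

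A reader might also infer that the sample size is wrong. This point does not show that: 138 is the correct arithmetic for the between-arm test that should be primary.

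**What to change.** 1. In Data Analysis, name as the co-primary analysis the between-arm difference (TCQ minus PT) in week-12 NRS and RMDQ, adjusted for the baseline score, with a 95% confidence interval. An unadjusted independent-samples comparison would also remove the contradiction; baseline adjustment is the better choice.
2. Report within-arm paired changes descriptively only.
3. In the Introduction, reword the primary hypothesis as the between-arm comparison and say how it relates to the non-inferiority hypothesis, so that it is clear whether the primary claim is superiority or non-inferiority. Align the purpose stated at the end of Sample Size.

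These are wording changes and need no new data. With 55 completers per arm, 138 enrolled still gives 80% power for d = 0.54 in a superiority comparison, but only if individuals are independent. The Randomization and Blinding section allocates four communities, two per arm. How the between-arm analysis should handle that is a separate point, and it may cost more than wording.

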**Methods:**

We will perform a single-blind randomized controlled trial on elderly people with chronic low back pain. 138 participants will be randomly assigned to the Tai Chi Quan group (60-min classes, three times per week for 12 weeks) or physical therapy group (10 min of evaluation and warm-up, 40 min of therapist-directed exercise therapy, and 10 min of relaxation, three times per week for 12 weeks) with an allocation of 1:1. The participants will be followed up for 40 weeks for the study of long-term effects. The primary outcomes include pain intensity and back-related function at 12 weeks. Secondary outcomes include lumbar quantitative sensory testing, balance, cognitive function, psychosocial function, cost-effectiveness, compliance and adverse events. We will perform the intention-to-treat analysis for withdrawal and missing data.

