## Study Design and Methods

### Study Design

The study is a single-blinded RCT of TCQ classes or grouped-PT for patients with CLBP (Figure 1. Study flow diagram). Eligible participants will be randomly assigned into the Tai Chi Quan group (TCQG) or physical therapy group (PTG). Both groups will perform exercises for 60 min three times a week for a total of 12 weeks. After the program, 40 weeks of follow-ups will be conducted.

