## Data Management and Analysis

### Data Management

After recruitment, the researchers will replace the participants’ names with numerical codes in order to protect their privacy. Their data will be collected at baseline and week 12, 26, and 52, respectively. Two professional data workers are responsible for entering their paper files into the same database and cross-checking them for data’s accuracy. Eventually, all paper files and encrypted electronic files will be kept and backed up by the researcher leader. These files will be maintained in storage for 3 years after completion of the study.

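### The follow-up ANOVA names no visits, deciding term or contrast, so its omnibus interaction cannot show whether TCQ outlasts PT

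*Protocol article*

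**What the plan says.** The Introduction ranks three hypotheses, and the last concerns durability: "The third hypothesis is that TCQ has a longer-term effect than PT". Study Design provides the observation time: "After the program, 40 weeks of follow-ups will be conducted", which after a 12-week programme ends at week 52. Data Management gives the visits: "Their data will be collected at baseline and week 12, 26, and 52, respectively". Table 1 attaches the follow-up label to weeks 26 and 52 only.

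Data Analysis assigns one method to this phase: "For the follow-ups phase, two-way repeated-measures analysis of variance (group × time) will be carried out to assess the differences of the primary outcomes", the outcomes being NRS and RMDQ. The threshold is general: "In all analyses, a *P*-value of <0.05 will be considered statistically significant". The section does not say whether the group term or the interaction decides, whether baseline or week 12 is in the model, or which week is compared. It does mention independent-samples t-tests, both generally for continuous variables (NRS and RMDQ among the examples) and for secondary outcomes. It ties none of them to week 52 or to the third hypothesis.

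**The concern.** A claim that one treatment lasts longer than another needs a contrast with a sign and a time. It could be the between-group difference at week 52, or the between-group difference in change from week 12 to week 52. A group × time interaction asks something else: whether the two mean profiles depart from parallel in any way. It has no sign, and a gap that closes counts the same as a gap that opens. The group main effect averages over whichever visits are in the model, so what it means depends on a choice the article leaves open.

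The Discussion presents the 40-week follow-up as a strength for comparing short- and long-term benefit, and it looks to the trial for evidence that TCQ is a durable alternative. If the interaction is the evidence, an early difference that has disappeared by week 52 could be reported as support. A benefit that is steady from week 12 to week 52 could be reported as no effect if baseline is left out.

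**Working it through.** **The plan's own figure.** Sample Size states "we assume that two-sided α error prob is equal to 0.05 and power is 0.8" and "Considering the effect size of RMDQ is 0.54 and 20% attrition rate, we need a minimum of 138 participants in this study". A two-sample t-test (noncentral t) with d = 0.54 needs 54.8, so 55 per arm or 110 in all. Then 110 / (1 − 0.20) = 137.5, rounded up to 138, or 69 per arm under 1:1 allocation. The stated figure is reproduced. It is sized for week 12, not for durability. After 20% attrition, 69 × 0.8 = 55.2, so n = 55 per arm is used below.

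**Assumptions not in the article.** Outcomes are in SD units with equal variances and the same correlation ρ between any two visits. The article gives no ρ, so 0.5 is taken, with 0.3 and 0.7 as the range. Participants are treated as independent.

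**Formula.** Let δ_t be the between-arm difference at visit t, and δ̄ its mean over the T visits in the model. Under these assumptions the interaction F has T − 1 and 108(T − 1) degrees of freedom and noncentrality

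λ = (n/2) × Σ(δ_t − δ̄)² / (1 − ρ) = 27.5 × Σ(δ_t − δ̄)² / 0.5.

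Only the spread of the differences enters. Their sign and order do not.

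**Results, ρ = 0.5, two-sided 0.05**

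| Difference at weeks 12, 26, 52 (SD) | Visits in model | Σ(δ_t − δ̄)² | λ | Significant, formula | Significant, simulation |
|---|---|---|---|---|---|
| Fading: 0.5, 0.25, 0 | baseline + 3 | 0.1719 | 9.45 | 72.9% | 73% |
| Emerging: 0, 0.25, 0.5 | baseline + 3 | 0.1719 | 9.45 | 72.9% | 72% |
| Fading | weeks 12, 26, 52 | 0.1250 | 6.88 | 64% | 64% |
| Fading | weeks 26, 52 | 0.0313 | 1.72 | 25.5% | 26% |
| Constant 0.54 | baseline + 3 | 0.2187 | 12.03 | 83.6% | 83% |
| Constant 0.54 | weeks 12, 26, 52 | 0 | 0 | 5% | 5% |

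First row worked out: the differences are 0, 0.5, 0.25, 0 with mean 0.1875. The sum of squares is 0.3125 − 4 × 0.1875² = 0.1719, and λ = 27.5 × 0.1719 / 0.5 = 9.45. The second row holds the same values in another order, so the two opposite truths have exactly the same chance of a significant result. A week-52 comparison in the fading case rejects 5% of the time, as it should.

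**Sensitivity to ρ.** For a gap fading as 0.54, 0.27, 0, simulated interaction rates at ρ = 0.3, 0.5, 0.7 are 63%, 81%, 96% with four visits and 55%, 70%, 92% with weeks 12, 26 and 52. The percentages move with ρ. The failure to distinguish fading from emerging does not.

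**Power, emerging case (true week-52 difference 0.5 SD, ρ = 0.5).**
- Four-visit interaction: 72% simulated (72.9% by formula).
- Unadjusted week-52 t-test: noncentrality 0.5 / √(2/55) = 2.62, giving 73% simulated (73.9% by formula).
- Week-52 comparison adjusted for baseline: residual SD √(1 − 0.5²) = 0.866, noncentrality 2.62 / 0.866 = 3.03, giving 84% simulated (85.1% by formula).

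The gain of roughly 11 percentage points over the unadjusted test comes from the baseline covariate.

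**The case against.** The best defence is that the method is attached to the follow-up phase and that Table 1 gives that label to weeks 26 and 52 alone. On that reading there are two visits, baseline is not averaged in, and the group main effect is the mean between-arm difference over follow-up, a reasonable long-term contrast. A constant 0.54 SD benefit would then be found by the main effect about 90% of the time, and a benefit confined to week 12 would give only about 5% on either term. This stands as a possible reading. The article does not choose it, though, and does not say that the main effect decides.

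It is also fair that contrasts after an ANOVA are often left to an analysis plan, which is not shown, and that a longer-term effect could mean slower loss of benefit, which is a group-by-time question. Even then the relevant quantity is a signed contrast, such as the change from week 12 to week 52, and not an omnibus test.

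Four stronger readings are tempting, and the documents do not support them:
- A reader might infer that the ANOVA is the wrong model. It is a legitimate one.
- A reader might infer that the omnibus test loses power. It does not in the case computed: 72% against 73% for an unadjusted week-52 test.
- A reader might infer that uneven visit spacing or missing visits invalidates it. Uneven spacing does not by itself violate sphericity, the results above arise with sphericity satisfied, and multiple imputation is planned.
- A reader might infer that the model certainly includes baseline, with a 3-df interaction. The article does not say so.

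**Conclusion.** The point holds as a mismatch between a stated hypothesis and its only assigned analysis. The third hypothesis is directional, while the planned method has no named visits, deciding term or contrast, and its interaction test cannot separate a vanishing benefit from an emerging one (about 73% against 72% with baseline in the model). The unstated choice of visits matters as much: the fading-benefit rate runs from about 73% to 64% to 26% with four, three or two visits, and the rate for a constant benefit from about 83% to 5% once baseline is dropped.

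The percentages rest on 55 per arm, an assumed correlation of 0.5, equal variances and independent participants. The fading-benefit rates are also not pure false positives, because that scenario contains real differences at weeks 12 and 26. They are misleading only if read as evidence of durability. This is worth correcting before analysis. It does not touch the week-12 co-primary comparison or the sample size.

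**What to change.** For the NRS scores and RMDQ, replace the follow-up ANOVA with a repeated-measures mixed model on weeks 12, 26 and 52, with the baseline score as covariate and group, visit and group × visit as fixed effects. State that the third hypothesis is tested by the baseline-adjusted between-group difference at week 52, and give its direction (lower scores favour TCQ on these scales). Name the between-group difference in change from week 12 to week 52 as supportive.

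This uses visits already scheduled and a model available in the named software. The cost is a few sentences and slightly more analysis work, and the team must commit in advance to one reading of a longer-term effect. The allocation of four communities, described under Randomization and Blinding, is a separate issue and should be dealt with on its own. A community random effect should not be added here, since two communities per arm would barely allow it to be estimated.
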